### Inclusion and exclusion criteria

Please refer to Table 1 for a listing of study inclusion and exclusion criteria. All subjects will be tested for photosensitivity as per the manufacturer’s user guide instructions. A 20-minute session of LED-RL phototherapy will be performed on the subject’s nondominant proximal anterior forearm, and evaluation for photosensitivity will occur 24 hours post LED-RL phototherapy. Criteria for photosensitivity include but are not limited to: warmth, erythema (redness), edema (swelling), rash, pain, or discomfort lasting more than 24 hours.

**Table 1 Tab1:** Study inclusion and exclusion criteria

Inclusion criteria	Exclusion criteria
• Healthy subjects of any sex, age, and ethnicity • Nondominant proximal anterior forearm is wide enough to ensure reproducible placement of light-emitting diode-red light (LED-RL) phototherapy or mock therapy hand-held unit • Available and willing to attend all clinic visits • Able and willing to give informed consent	• Subjects on any photosensitizing medications (i.e. lithium, melatonin, phenothiazine antipsychotics, antibiotics) • Subjects with light-sensitive conditions • Subjects with diabetes mellitus (DM) • Subjects with a history of skin cancer: basal cell carcinoma (BCC), squamous cell carcinoma (SCC), or melanoma • Subjects with systemic lupus erythematosus (SLE) • Subjects with any other medical condition that could be compromised by exposure to the proposed procedure • Subjects with open wounds on the nondominant proximal anterior forearm • Subjects with fibrotic skin disease or other skin conditions on the nondominant proximal anterior forearm • Subjects with tattoos that cover the procedure site on the nondominant proximal anterior forearm

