### Specifications of LED-RL phototherapy and mock therapy hand-held unit

The LED-RL light source is a commercially available Omnilux New-U hand-held LED-RL phototherapy unit (provided by Photo Therapeutics, Carlsbad, CA, USA), and is FDA-cleared for treatment of periorbital rhytides (crow’s feet) and may be placed in direct contact with the skin [23]. The mock therapy unit, also provided by Photo Therapeutics, Carlsbad, CA, USA, only generates warmth and does not emit LED-RL. The LED has a 4.7 cm × 6.1 cm rectangular aperture and emits visible red light (633 nm ± 30 nm) at a power density of 360.2 W/m^2^ at room temperature in direct contact with the photometer.

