### Study procedure

The study procedure for subjects receiving LED-RL phototherapy and for subjects receiving mock therapy is identical with the exception of utilizing the LED-RL phototherapy unit or the mock therapy unit for the randomized subjects in their respective groups. After confirming subject identity, screening for study eligibility, and obtaining written Institutional Review Board (IRB)-approved informed consent, the subject will be taken to a private clinic examination room at the Dermatology Clinic in Sacramento VA Medical Center. The subject’s nondominant proximal anterior forearm will be cleaned with alcohol pads. A surgical marking pen will be used to outline the procedure area at the start and completion of every visit. The LED-RL phototherapy or mock therapy hand-held unit will be held in place and in direct contact with the clean area using nonadhesive tape (ACE elastic bandage or similar) during the procedure. All subjects will be provided with protective eyewear to use at LED-RL phototherapy and mock therapy sessions. The research team will be observing the procedure and assessing for any safety issues during and immediately post-procedure. Photographs will be taken pre-and post-procedure at each clinic visit to record and assess for common expected procedural side effects and adverse events, and to ensure uniformity of procedure location at every clinic visit.

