### Blinding

This is a single-blind study, and the subjects will be blinded to the procedure (LED-RL phototherapy or mock therapy). The PI and clinical research coordinators (DH and EK) will be aware of the randomization.

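### The photosensitivity test lets every mock subject experience the real red-light unit beforehand, which puts the trial's only blinding at risk and narrows the 1-in-10 safety statement

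*Protocol article*

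**What the plan says.** - **Test (Inclusion and exclusion criteria).** "All subjects will be tested for photosensitivity as per the manufacturer’s user guide instructions". The exposure is specified: "A 20-minute session of LED-RL phototherapy will be performed on the subject’s nondominant proximal anterior forearm". The reading is fixed: "evaluation for photosensitivity will occur 24 hours post LED-RL phototherapy". Criteria for a positive test include redness, swelling, pain or discomfort that persists beyond a day.
- **Site (Study procedure).** "The subject’s nondominant proximal anterior forearm will be cleaned with alcohol pads", and the unit is then strapped to the skin there with an elastic bandage. Protective eyewear is provided at active and mock sessions. The two arms differ only in the unit used.
- **Units (Specifications of LED-RL phototherapy and mock therapy hand-held unit).** The active unit "emits visible red light (633 nm ± 30 nm) at a power density of 360.2 W/m^2^ at room temperature". The mock unit "only generates warmth and does not emit LED-RL".
- **Blinding (Blinding).** "the subjects will be blinded to the procedure". The investigator and the coordinators know the allocation.
- **Use of the data.** Safety assessment has subjects record side effects and adverse events in a diary. Statistical analysis compares the rates of both between arms. Study design and subject population counts pain, altered sensation and redness beyond 24 hours as toxicities, lists warmth as an expected side effect, and aims to conclude with 95% confidence that fewer than 1 person in 10 will have an adverse event.

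**The concern.** A subject who has never met the active device has little basis for judging whether a warm unit under a bandage is real. The screening test supplies that basis: each subject has experienced the genuine light-emitting unit before the first study session. If the mock then looks or feels different, a mock subject can tell. An active subject can likewise confirm that the unit is the same as before.

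This matters because subject blinding is the only blinding in the trial and several compared events depend wholly on what the subject reports. Subjects who believe they have the active unit may report more warmth, pain or altered sensation, and those who recognise the mock may report less. That would widen the difference between arms for reasons unrelated to the light.

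A second consequence concerns scope. The same device, body region and type of reaction count as an eligibility finding at the test and as a dose-limiting toxicity in the study. If reactors are removed first, the safety rate describes a pre-selected group, whereas the sample-size passage states it without condition.

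**Working it through.** **1. Who is affected.** With four dose groups of three active and two mock subjects, plus the expansion cohort:
- mock: 4 × 2 + 18 = 26
- active: 4 × 3 + 27 = 39
- total: 65, matching the stated maximum. The 26 is reached only if all four dose groups run.

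**2. Size of the test exposure.** No fluence is stated for the test. Fluence (J/cm²) = power density (W/cm²) × time (s).

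The plan's one pairing of fluence and time is 640 J/cm² in 2 hours (Study design and subject population). The stated power density does not reproduce it:
- 360.2 W/m² = 0.03602 W/cm², and 0.03602 × 7200 = 259.3 J/cm², not 640
- 640 J/cm² in 2 hours implies 640 / 7200 = 0.08889 W/cm² = 888.9 W/m²
- the two differ by 888.9 / 360.2 ≈ 2.5

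The 20-minute (1200 s) dose is therefore a range:
- stated power density: 0.03602 × 1200 = 43.2 J/cm²
- rate implied by 640 in 2 hours: 0.08889 × 1200 = 106.7 J/cm²

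**3. That exposure against the study doses.**

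| Comparator | J/cm² | Test as % (43.2 to 106.7) |
|---|---|---|
| One session at 160 | 160 | 27.0% to 66.7% |
| Nine sessions at 160 | 1440 | 3.0% to 7.4% |
| One session at 640 | 640 | 6.8% to 16.7% |
| Nine sessions at 640 | 5760 | 0.8% to 1.9% |

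The nine-session course is the relevant comparator, because that is what the active arm receives and the mock arm does not.

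**4. Blinding.** Side by side, the sections give visible red light at the test, no LED-RL from the mock, the same forearm region for both, and an outcome recorded by the blinded party. What stands between the subject and recognition is eyewear described only as protective and a bandage that holds the unit in place. Neither is described as hiding the light. The documents contain nothing from which a rate of correct guessing, or the resulting bias, can be computed.

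**5. The 1-in-10 statement.** The plan's figure is reproduced: with no events in 30 active subjects, the rule of three gives 3 / 30 = 0.10 (exact: 1 − 0.05^(1/30) = 0.095). If all 30 had first tested negative, that bound applies to test-negative people. Let r be the share of screened people who react to the test, and count a test reaction as an event. The corresponding bound for everyone screened is then r + (1 − r) × 0.10, taking r as known. This exceeds 0.10 for any r above zero. The documents give no value for r.

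**The case against.** A reader might infer that the test contaminates the control arm. The documents do not support that. The exposure is single, equal in both arms and below the lowest study dose, and it is read at 24 hours. The randomized contrast of nine active against nine mock sessions is intact. Nor do the documents say that the test uses the identical marked area; only the forearm region is shared.

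A reader might also infer that blinding is broken. That too goes beyond the text. The unit sits against the skin under a bandage, eyewear is provided, and the mock produces warmth. Eyewear opacity and any glow from the mock are not described, and a condensed article may leave such details to the full protocol. If the light is visible at all, the arms differ at every session whether or not there was a test; the test adds a reference for comparison. What remains is that the plan as written creates that reference and describes no step to offset it.

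The reach is limited as well. The maximally tolerated dose and the 1-in-10 statement do not rest on the mock comparison, and burns, blisters, ulceration and persistent redness are visible to staff and photographed. The blinding risk bears on the subjective items in the between-arm test.

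Finally, every trial's rate is conditional on its eligibility criteria, and the test is openly described. That is fair. Here, though, the screen uses the study device and overlaps the study's own toxicities, so the condition bears directly on the conclusion and should be stated. The article does not say explicitly that reactors are excluded or how they are reported.

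**Conclusion.** The point holds as a risk to subject blinding and as a limit on the scope of the safety conclusion. Up to 26 mock subjects experience the real unit before a mock that emits no LED-RL, with no described masking of the light, in a trial whose only blinded party reports part of the outcome. The resulting bias cannot be sized from the documents and is confined to the self-reported items.

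Controls are not LED-RL-naive in the forearm region, by 43 to 107 J/cm². That is 3.0% to 7.4% of the course at 160 J/cm² and 0.8% to 1.9% at 640 J/cm², so it does not undermine the contrast.

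Assumptions:
- the test precedes the first study session, as its place under eligibility and the order in Study procedure suggest
- reactors are excluded, which that placement implies but the text does not state
- the mock can be told apart from the active unit if the light is not hidden

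**What to change.** 1. During the test and all sessions in both arms, hide the light in the same way, with an opaque cover over the unit and its edges, light-blocking eyewear, or both. Say so in Study procedure and Blinding.
2. Ask each subject to guess the allocation after session 1 and at the end, and report the guesses by arm.
3. State whether test reactors are excluded, and report how many people were tested and how many reacted.
4. Word the final adverse-event rate, including the 1-in-10 statement, as conditional on a negative photosensitivity test.
5. Reconcile the stated power density with the pairing of 640 J/cm² and 2 hours, so that the fluence of the test can be given.

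The cost is covers or eyewear, one added question asked twice, and some wording. The test site should stay as it is: moving it would alter a safety screen specified by the manufacturer and would do nothing for blinding.

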### Specifications of LED-RL phototherapy and mock therapy hand-held unit

The LED-RL light source is a commercially available Omnilux New-U hand-held LED-RL phototherapy unit (provided by Photo Therapeutics, Carlsbad, CA, USA), and is FDA-cleared for treatment of periorbital rhytides (crow’s feet) and may be placed in direct contact with the skin [23]. The mock therapy unit, also provided by Photo Therapeutics, Carlsbad, CA, USA, only generates warmth and does not emit LED-RL. The LED has a 4.7 cm × 6.1 cm rectangular aperture and emits visible red light (633 nm ± 30 nm) at a power density of 360.2 W/m^2^ at room temperature in direct contact with the photometer.

### Study procedure

The study procedure for subjects receiving LED-RL phototherapy and for subjects receiving mock therapy is identical with the exception of utilizing the LED-RL phototherapy unit or the mock therapy unit for the randomized subjects in their respective groups. After confirming subject identity, screening for study eligibility, and obtaining written Institutional Review Board (IRB)-approved informed consent, the subject will be taken to a private clinic examination room at the Dermatology Clinic in Sacramento VA Medical Center. The subject’s nondominant proximal anterior forearm will be cleaned with alcohol pads. A surgical marking pen will be used to outline the procedure area at the start and completion of every visit. The LED-RL phototherapy or mock therapy hand-held unit will be held in place and in direct contact with the clean area using nonadhesive tape (ACE elastic bandage or similar) during the procedure. All subjects will be provided with protective eyewear to use at LED-RL phototherapy and mock therapy sessions. The research team will be observing the procedure and assessing for any safety issues during and immediately post-procedure. Photographs will be taken pre-and post-procedure at each clinic visit to record and assess for common expected procedural side effects and adverse events, and to ensure uniformity of procedure location at every clinic visit.

### Safety assessment

All subjects will be asked to record any common expected procedural side effects and adverse events in a subject diary of adverse events for the entire duration of study participation. A review of the subject’s diary will occur at each clinic visit prior to the start of the procedure. Subjects will be called weekly to monitor for any adverse events. Subjects with adverse events will receive standard medical care outside of the scope of this study. Ancillary and post-study care is available at the General Dermatology Clinic, Sacramento VA Medical Center, but no additional compensation will be provided to those who suffer harm from study participation. All common expected procedural side effects and adverse events will be described in the Case Report Form. The Data Safety Monitoring Board, which includes three board-certified dermatologists, one phototherapy nurse, and two clinical research coordinators, will convene monthly to review and assess any study safety issues. The principal investigator (PI: JJ) has access to interim results and may make the decision to stop a subject from study participation due to safety reasons.

### Randomization

Randomization will be performed by clinical research coordinators via the www.randomizer.org website. For assignment of study groups, Arabic numerals “1,” “2,” “3,” “4,” and “5” will be generated at random. Subjects assigned to “1” will be in group 1 (160 J/cm^2^), “2” will be in group 2 (320 J/cm^2^), “3” will be in group 3 (480 J/cm^2^), “4” will be in group 4 (640 J/cm^2^), and “5” will be in group 5 (640 J/cm^2^ or MTD). For assignment of LED-RL phototherapy and mock therapy, Arabic numerals “1” and “2” will be generated at random. Subjects assigned to “1” will receive LED-RL phototherapy and subjects assigned to “2” will receive mock therapy. A study randomization flowchart is shown in Fig. 1.

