**Methods/design:**

This is a single-blind, dose escalation, randomized controlled, phase I study to evaluate the safety of high-fluence LED-RL on human skin. The protocol for dose escalation requires subjects be enrolled sequentially in groups of five. Within each group, three subjects will be randomized to LED-RL phototherapy and two subjects randomized to mock therapy. Subjects in group 1 randomized to LED-RL phototherapy will receive the maximum recommended starting dose (160 J/cm^2^). LED-RL dose will be escalated in subsequent groups (320 J/cm^2^, 480 J/cm^2^ and 640 J/cm^2^). The maximally tolerated dose (MTD) is defined as the dose level below the dose producing unacceptable but reversible toxicity and is considered to be the upper limit of subject tolerance. After either a MTD has been established, or the study endpoint of 640 J/cm^2^ has been achieved, an additional 27 LED-RL phototherapy subjects (for a total of 30) and 18 mock therapy subjects (for a total of 20) (determined randomly) will be enrolled. Each subject will receive a total of nine procedures, three times per week for three consecutive weeks.

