### Study design and subject population

This is a single-blind, dose escalation, randomized controlled, phase I study to evaluate the safety of high-fluence LED-RL phototherapy on human skin. The maximum recommended starting dose (MRSD) of 160 J/cm^2^ is based upon previously published maximum doses of LED-RL phototherapy used in clinical studies that demonstrated clinical safety with no adverse events [18, 19]. The study endpoint of 640 J/cm^2^ was chosen due to feasibility, as this dose corresponds to 2 hours of LED-RL phototherapy, and we anticipate decreased subject compliance with LED-RL exposures longer than 2 hours in duration. Additionally in prior studies, the 640 J/cm^2^ dose demonstrated increased anti-fibrotic properties in vitro compared to lower doses of LED-RL [17].

The protocol for dose escalation requires subjects to be enrolled sequentially in groups of five (three subjects randomized to LED-RL phototherapy and two subjects randomized to mock therapy). As this is a single-blind study, subjects will be blinded to the procedure (LED-RL phototherapy or mock therapy).

Subjects in group 1 randomized to LED-RL phototherapy will receive the MSRD of 160 J/cm^2^. The LED-RL dose will be escalated in subsequent groups using the classical method for dose escalation as described by Spilker: starting with dose (X) increased by an equal amount (in this instance: X = 160 J/cm^2^, 2X = 320 J/cm^2^, 3X = 480 J/cm^2^, and 4X = 640 J/cm^2^) [20]. Common expected procedural side effects are mild and are expected to last less than 24 hours, which include warmth, redness (erythema), and swelling (edema). The MTD is defined as the dose level below the dose producing unacceptable but reversible toxicity and is considered to be the upper limit of subject tolerance. Unacceptable but reversible toxicities (adverse events) for this study include: second-degree or higher skin burning or blistering, erythema lasting more than 24 hours, severe swelling, pain, ulceration, change in sensation, and/or muscle weakness. If one or more subject experiences any of these adverse events, then this is the dose one above the MTD, and we will not proceed with this dose or escalate the dose.

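### The Randomization section assigns dose groups by a random numeral, which contradicts the sequential dose escalation described elsewhere in the protocol

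*Protocol article*

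**What the plan says.** The Randomization section describes two random draws. The first concerns the dose group: "For assignment of study groups, Arabic numerals “1,” “2,” “3,” “4,” and “5” will be generated at random". Numerals one to four are tied to 160, 320, 480 and 640 J/cm², and a subject who draws the fifth "will be in group 5 (640 J/cm^2^ or MTD". The second concerns the arm: "For assignment of LED-RL phototherapy and mock therapy, Arabic numerals “1” and “2” will be generated at random". No weights are given for either draw, and nothing limits the first draw to the group currently open.

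The rest of the document describes a different scheme:

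- Study design and subject population: "The protocol for dose escalation requires subjects to be enrolled sequentially in groups of five", and "The LED-RL dose will be escalated in subsequent groups using the classical method for dose escalation". One or more listed adverse events at a dose marks that dose as one step above the MTD and ends escalation.
- Abstract, Methods/design: the same sequential rule, with only the arm randomized inside a group: "Within each group, three subjects will be randomized to LED-RL phototherapy and two subjects randomized to mock therapy".
- Study design and subject population: the further 27 LED-RL and 18 mock subjects enter only once an MTD has been established or 640 J/cm² has been reached. The maximum sample size is 65.

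**The concern.** A dose group cannot both be filled in order, after the group below it has been observed, and be assigned by chance. Because the arm has its own draw, the group draw cannot be read as a loose description of arm allocation. It assigns the dose level.

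The Randomization section is the text that the coordinators who allocate subjects would work from. The Background section says that, to the authors' knowledge, no clinical trial has established the safety of fluences above 160 J/cm², whereas the starting dose does have cited clinical data. The order of exposure is therefore a main safeguard of this phase I design. Two things are at stake if the text is followed literally: subjects could be exposed to a level before the one below has been observed, and the expansion cohort that supports the safety claim might not reach its planned size.

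**Working it through.** **The plan's own figures.** From the section on study design and subject population:

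- Total: 4 groups × 5 + (27 + 18) = 65, which matches the stated maximum.
- Final dose: 3 + 27 = 30 LED-RL and 2 + 18 = 20 mock, which match the stated totals.
- Safety claim with zero events in 30: rule of three 3/30 = 10%; exact one-sided 95% upper limit 1 − 0.05^(1/30) = 9.5%.

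The planned sizes are thus 5, 5, 5, 5 and 45, and the 30 pools the three LED-RL subjects from the escalation group at the final dose with the 27 added later.

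**Literal reading of the Randomization section.** Assumptions: one numeral per subject, each of the five equally likely. The arm draw is taken as 1:1 (two numerals, no weights stated) or 3:2 (the ratio stated elsewhere).

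- First subject in groups 2 to 4, whose doses are fixed above 160 J/cm²: 3/5 = 60%.
- First subject in groups 2 to 4 and on active light: 0.60 × 0.5 = 30% (1:1) to 0.60 × 0.6 = 36% (3:2).
- First subject in group 5, whose dose is not yet defined: 1/5 = 20%.
- All of the first five subjects in group 1: 0.2^5 = 0.0003. Under sequential enrolment this is 1.
- Expected group size: 65/5 = 13 in every group.
- Groups 4 and 5 pooled: 2 × 13 = 26 subjects, of whom 26 × 0.5 = 13 to 26 × 0.6 = 15.6, about 16, are on LED-RL.
- Upper limit with zero events: 1 − 0.05^(1/13) = 20.6%; 1 − 0.05^(1/16) = 17.1%. Both exceed 10%.

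**Alternative assumption.** Suppose the random numbers fill a list of the 65 planned places, so that the sizes stay at 5/5/5/5/45.

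- First subject in groups 2 to 4: 15/65 = 23%; on active light there (3 of each 5): 9/65 = 14%.
- First subject in group 5: 45/65 = 69%.
- All of the first five in group 1: 1/C(65,5) = 1.2 × 10⁻⁷.

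Here the 30 LED-RL subjects and the 9.5% limit are kept, but the order of enrolment still contradicts the escalation, and most early subjects would have no defined dose.

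**After the correction.** With the arm alone randomized 3:2 in groups filled in order, the sizes are 5, 5, 5, 5 and 45, and the first five subjects are all in group 1. No sample-size figure changes.

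**The case against.** The strongest reply is that the Randomization text may simply be a slip. The abstract, the study endpoints and the study design section all point to escalation. The text does not say that the numeral is drawn for each subject at entry, gives no equal weights, and does not say when each group is treated. Subjects could in principle be drawn into groups from a pool and the groups still be treated in order. The section also refers to a flowchart that is not available here.

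Much of this stands, and it limits the claim. A reader might infer that the trial has no escalation, or that first subjects will be put at the highest fluence. The documents do not support either: both need the literal per-subject reading, and the stated design is sequential. Three larger figures are also tempting and should not be used:

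- An 80% chance that the first subject is above the starting dose (4/5). This counts group 5, whose dose is undefined at that stage.
- A 48% chance of active light above the starting dose (0.80 × 0.60). This again counts group 5, and joins the literal group draw to a 3:2 ratio that the Randomization section does not state.
- An upper limit of 31% (zero events in about 8 LED-RL subjects, from 13 × 0.6). This leaves out group 4, although the plan's 30 includes the escalation subjects at the final dose.

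What does not stand is that evident intent removes the problem. Drawing groups from a pool does not fit enrolment in sequence. The flowchart's caption repeats only the MTD and toxicity definitions. Condensing a protocol into an article explains omissions, but not a stated allocation rule that conflicts with three other statements.

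**Conclusion.** The Randomization section is wrong as it stands. Random assignment to dose groups 1 to 5 is incompatible with sequential groups of five, with the rule that ends escalation, and with an expansion cohort whose dose depends on the earlier groups. That conclusion rests on the text alone.

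The size of the harm is conditional on literal use and on the assumed draw. The chance that the first subject is on active light at a fixed dose above 160 J/cm² is 30% to 36% with equal per-subject draws, and about 14% if 65 fixed places are filled at random. The loss of precision, to an upper limit of about 17% to 21%, applies only to the equal-draw reading. There, the plan's conclusion of fewer than 1 in 10 with 95% confidence would not be met even with zero events. Enrolment had already begun in January 2016 (Study status), so the point should be settled, not left to interpretation.

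**What to change.** Reconcile the Randomization section with the abstract and the section on study design and subject population:

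- Remove the random draw of group 1 to 5.
- Set group membership by order of enrolment into the group currently open.
- Use the randomizer only for LED-RL versus mock within that group, and state the 3:2 ratio there.
- Use the group 5 list only after the escalation stage has closed.
- Have the sponsor confirm and report how subjects already enrolled were assigned to group and arm.

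This applies the document's own enrolment rule and changes no dose. The cost is one rewritten paragraph and possibly a new allocation list, with no extra subjects. It is higher only if a random group list has already been used. In that case the allocations made under it must be documented and taken into account in the analysis.
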